#### *Control participants - usual care group (UCG)*

The usual care group (UCG) participants will receive standard or usual care for sleep disorders based on the usual practice in the community pharmacy. Australian community pharmacies usually follow the Pharmaceutical Society of Australia’s recommended practice [45], which includes supplying ‘Pharmacy medicine’, ‘Pharmacist only medicine’, complementary medicine or other over-the-counter (OTC) medicines for sleep-related disorders, if indicated. At baseline, follow the same protocol as in the intervention group, study eligibility (Table 1) will be checked and inform consent will be obtained before the participants complete the ‘Initial Pharmacy Visit’ questionnaires. Baseline demographic and assessments will be completed for comparisons with the ICG participants. The UCG participants will be followed-up after two weeks by the study researcher via email or mail to complete the ‘End of Study’ questionnaires.

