**Eligibility criteria**	
**Inclusion**	**Exclusion**
• Aged ≥ 18 years old	• Aged < 18 years old
• Attend a participating pharmacy as a ‘walk-in customer’ seeking help for sleep-related disorders or having symptoms of sleep disorders.	• Not able to speak, read and write in English, or not fluent in English and cannot arrange for a translator themselves or a translator is not available.
	• Unable to complete the screening (in the pharmacist’s opinion).
	• Refuse to give consent.
	• Pregnant.
	• Currently under treatment with continuous positive airway pressure (CPAP)

The actigraph is a useful device for monitoring sleep-related disorders, but literature suggests that it should be used in conjunction with other parameters, such as sleep diaries [31,42] as both may complement each other by providing objective and subjective data, respectively. Therefore, participants will be provided with an intervention package, which includes:

1. An actigraph (SBV2 Readiband™) to be worn 24-hours a day for seven days before participants revisit the pharmacy for their first follow-up, and then for a further seven days after the first follow-up before returning to the pharmacy for final assessment.

2. A sleep diary [43] to self-record 14 days of bedtime, wake time, time to fall asleep, number of nocturnal awakenings and total sleep time, plus information related to sleep-hygiene, lifestyle and other factors that may interrupt sleep.

3. Educational information about sleep disorders, sleep health management, sleep hygiene and healthy lifestyle to improve sleep (via access link to a website: http://sleepproblemandyou.wordpress.com/ which is developed specifically for this study). The web address will be provided to each participants.

One complete study duration for a participant in the intervention group is two weeks with follow-ups at two time points; week 1 (day 8) and week 2 (day 15). At both time points, pharmacy staff will analyse the data downloaded from the actigraph using Sleep Consultant™ software to generate an on-the-spot individualise report of sleep/wake patterns and they will also assess the self-report information from the sleep diary.

##### 

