**Follow-up 1** The participants will receive sleep advice and possible solutions focusing on behavioural strategies such as sleep hygiene, change of lifestyle, daily alcohol and caffeinated drinks consumption and activities before going to sleep, based on data gained from both parameters. Any requests for sleep medicine (‘Pharmacist only medicine’ or ‘Pharmacy medicine’) will follow the pharmacy’s standard practice. After this session, the participants will continue to wear the actigraph plus complete the sleep diary for another seven days.

##### 

**Follow-up 2 / end of study** Participants’ first (pre) and second (post) individual sleep reports will be compared to assess any particular improvement in their sleep condition after receiving sleep advice and possible solution during the first follow-up. Participants will also complete the ‘End of Study’ questionnaires. In certain circumstances (see the ‘Protocol to refer participant to a general practitioner’ subsection), pharmacists can recommend a GP referral for further examination.

##### 

**Protocol to refer participant to a general practitioner (GP) at the end of study** In these circumstances: (1) if the sleep efficiency percentage (SE%) is below 85% at the end of study (normal SE% for adult if measure using actigraphy is 85% and above) [41,44], and (2) if analysis of the data collected appears to indicate that he/she may be at risk of having/developing sleep-related problems and has reported symptoms such as:

• choking or suffocating during sleep

• stopping breathing when sleep

• snoring during sleep

• excessive daytime sleepiness

• difficulty falling asleep at night

• having problems waking up in the morning

• falling asleep too early at night

• waking up too early at night

• fatigue and having difficulty concentrating on daily tasks

• experiencing unpleasant sensations with an urge to move their limbs

Above symptoms may be indicative of another sleep disorders, specifically OSA, narcolepsy, a circadian rhythm disorder, restless legs syndromes or a primary mood disorder.

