### Study measurements and outcomes

#### *Study measurements*

Assessments will be conducted at three times points – baseline, week 1 and week 2 (Table 2). At baseline upon recruitment, participants will be assisted to complete the self-administered ‘Initial Pharmacy Visit’ questionnaires, comprise of:

• Demographic and lifestyle information, which includes sleep environment, smoking, alcohol consumption and caffeinated drinks intake, modified from the validated ‘Pharmacy Tool for Assessment of Sleep Health - POTASH’ [24].

• Health-related quality of life (HRQOL) assessment using validated WHO-Five Well Being Index (version 1998) [46,47].

• Sleep health assessment using a set of survey instruments adapted from POTASH [24]: Epworth Sleepiness Scale (ESS) [48,49], Insomnia Severity Index (ISI) [50], Multivariate Apnea Prediction Index (MAPI) [51] and International Restless Legs Syndrome Study Group (IRLSSG) [52].

• Community pharmacy survey: 14 questions using a 5-point Likert-type scale from 1 (strongly disagree) to 5 (strongly agree), and one open ended question.

**Table 2 T2:** Summary of measurements and study outcomes

**Measurements**	**Instruments**	**Group**	**T0**	**T1**	**T2**	**Outcome**	
Surveys/measuring tools							
Socio-demographic and lifestyle	Questionnaire	ICG, UCG	x				2˚
Health-related quality of life ^I,E^	WHO-5 Well-being index (1998)	ICG, UCG	x		x	1˚	
Sleep scale scores ^I,E^	ESS, ISI, MAPI, IRLSSG	ICG, UCG	x		x	1˚	
Community pharmacy survey ^I^	Questionnaire	ICG, UCG	x				2˚
Close-out survey ^E^	Questionnaire	ICG, UCG			x	1˚	2˚
Sleep parameters assessment							
SE%	Actigraph only	ICG		x	x	1˚	
TST, NWAK, SOL	Actigraph and sleep	ICG		x	x	1˚	
	diary						
Other factors that may interrupt sleep	Sleep diary only	ICG		x	x	1˚	
Pharmacy survey							
Close-out survey for pharmacy	Questionnaire	Pharmacists, pharmacy staff			x		2˚

T0 = baseline, T1 = 1 week after baseline, T2 = 2 weeks after baseline.

ICG: intervention care group; UCG: usual care group.

ESS: Epworth Sleepiness Scale; ISI: Insomnia Severity Index; MAPI: Multivariate Apnea Prediction Index; IRLSSG: International Restless Legs Syndrome Study Group.

SE%: Percentage of sleep efficiency; TST: Total sleep time per-24 hour period; NWAK: Number of nocturnal awakenings; SOL: Sleep onset latency.

1˚: Primary outcome; 2˚: Secondary outcome.

I: ‘Initial Pharmacy Visit’ Questionnaires; E: ‘End of Study’ Questionnaires.

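### The week-2 questionnaires behind the between-group primary outcomes reach the two groups by different routes, so a route effect cannot be separated from the intervention effect

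*Protocol article*

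**What the plan says.** **Baseline.** Both groups complete the Initial Pharmacy Visit questionnaires under one procedure. The usual care section reads "At baseline, follow the same protocol as in the intervention group", and Study measurements says that "participants will be assisted to complete the self-administered" forms.

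**Week 2, usual care group (UCG).** The section on control participants states: "The UCG participants will be followed-up after two weeks by the study researcher via email or mail to complete" the End of Study questionnaires.

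**Week 2, intervention care group (ICG).** Participants wear the actigraph "for a further seven days after the first follow-up before returning to the pharmacy for final assessment" (intervention-group section, below Table 1). The same section adds: "At both time points, pharmacy staff will analyse the data downloaded from the actigraph". Under Follow-up 2 / end of study, the "first (pre) and second (post) individual sleep reports will be compared to assess any particular improvement in their sleep condition after receiving sleep advice", and then: "Participants will also complete the ‘End of Study’ questionnaires. In certain circumstances". One week before, under Follow-up 1: "The participants will receive sleep advice and possible solutions focusing on behavioural strategies such as sleep hygiene".

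**What the forms carry.** Study outcomes makes changes in WHO-5 (1a) and in ESS, ISI, MAPI and IRLSSG (1b) primary, compared between and within the groups. The close-out survey is in the same pack for both groups. Table 2 shows actigraph and diary measures for the ICG only.

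**The concern.** All five instruments in outcomes 1a and 1b are self-reported. Answers to such instruments can depend on where they are given, who asks, and who will read them. A participant who answers at the pharmacy that provided the service may answer differently from one who answers at home to a researcher. If the setting differs by group at the final assessment, any such difference enters the group comparison and looks like an effect of the service.

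The main effectiveness question is at stake, because these questionnaires supply the only between-group primary comparison of sleep and well-being. The close-out opinions and willingness to pay share the problem if they are compared between groups. So does secondary outcome 2, which is stated as a between-group comparison at week 2.

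**Working it through.** **1. Routes side by side**

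| Group | Baseline | Week 2 |
|---|---|---|
| ICG | Pharmacy visit, assisted | Pharmacy visit for final assessment (natural reading) |
| UCG | Same procedure | Remote, from the researcher by email or post |

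**2. Does change from baseline remove the difference?** Let δ be the true effect on a scale. Let m0 be the shift due to the baseline procedure (same in both groups), mP the shift from week-2 collection at the pharmacy, and mR the shift from remote collection. The difference in mean change is

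δ + (mP − m0) − (mR − m0) = δ + (mP − mR).

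The baseline term drops out. The week-2 term b = mP − mR stays. This does not depend on whether the ICG is assisted at week 2 as it was at baseline.

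**3. Can the analysis remove it?** Data analysis plans independent and paired t-tests. A richer model would not help: under the stated procedures, an indicator for route takes the same value as the indicator for group in every participant. Only the sum δ + b can be estimated. No objective measure is taken in both groups to corroborate a questionnaire difference.

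**4. Which outcomes are affected?** Outcomes 1a and 1b are, in their between-group part. Outcomes 1c and 2a (actigraphy, and actigraphy against diary) are ICG-only and are not, although the diary is self-reported.

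**5. What would a shift of a given size do?** Inputs:
- n = 25 per group (Sample size). This is used only as the number analysed. The protocol justifies it by a 20% difference between actigraphy and diary and gives no SD, so it cannot be rebuilt. The recruitment total does follow: 2 × 25 × 1.10 = 55.
- α = 0.05 (Data analysis). Sidedness is not stated; two-sided is assumed.
- b in SD units of the score tested. **Assumed**, as the documents give no value.
- δ = 0, equal SDs, independent participants.

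Formulas: df = 2 × 25 − 2 = 48; critical value 2.01; noncentrality λ = b√(n/2) = b√12.5 = 3.536b. The rejection probability is P(T > 2.01) + P(T < −2.01), with T noncentral t on 48 df.

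| Assumed b (SD) | λ | Rejection probability |
|---|---|---|
| 0 | 0 | 5.0% |
| 0.1 | 0.354 | 6.4% |
| 0.2 | 0.707 | 10.7% |
| 0.3 | 1.061 | 18.0% |
| 0.5 | 1.768 | 41% |

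The probabilities are per scale. Because the test is two-sided, they are the same for a shift in either direction.

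**The case against.** **The setting of ICG completion is a reading.** No single sentence says that the ICG fills in the forms in the pharmacy. That stands as a limit. But the return visit is for final assessment, and the questionnaires are listed under that visit, so this is the natural reading. If something else was meant, the same edit settles it.

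**Stronger readings are not supported.**
- A reader might infer that ICG participants answer after seeing their report, in front of the staff who advised them. The text puts the comparison of reports in the passive and says only that participants also complete the forms. The order within the visit, and any supervision, are not fixed. Only the week-1 advice certainly comes first.
- A reader might infer that only the UCG changes mode between baseline and week 2. Assistance is stated at baseline only, so the ICG may change too, from assisted to unaided.
- A reader might infer that the groups answer at different times. Table 2 puts the final time point two weeks after baseline for both. Different return times or response rates are possible but not documented.
- A reader might set the assumed shift against the difference that 25 per group can detect. The protocol states no such difference for these scales, and its sample size rests on another contrast.

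**Other weaknesses remain.** Allocation follows the pharmacy attended and is not randomised, and participants know what they received. Matching the route cures neither, and the 5% starting point in the table holds only if the test is otherwise valid. This limits the gain. It does not excuse the asymmetry: a pragmatic design explains differences in care, not in how the outcome is measured.

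**The fix may have a side effect.** Pharmacists consider GP referral at the end of the study from collected data and reported symptoms. Whether the End of Study scales feed that step is not said. If they do, sending them to the researcher would take them out of it.

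**Conclusion.** The point holds for the between-group primary outcomes 1a and 1b. At week 2 the route of collection differs by group, change scores do not cancel it, and no analysis of the planned data can separate it from the intervention effect. It extends to the close-out opinions and willingness to pay only where these are compared between groups.

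The documents establish a risk of bias, not its size or direction. The 11% to 18% rejection rate illustrates an assumed shift of 0.2 to 0.3 SD with 25 per group and no true effect; it does not estimate what will happen in this trial. The conclusion rests on the ICG completing the forms at the pharmacy visit. It needs no assumption about the order of events at that visit. This is an avoidable weakness in the main effectiveness comparison and is worth correcting, although it is not the only source of bias there.

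**What to change.** Use one route and one window for the End of Study questionnaires in both groups. The study researcher sends them by email or post at day 15 to the ICG as well as the UCG, and receives them directly.

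If the ICG forms stay at the pharmacy visit, state at minimum that participants complete them unaided, before the week-2 report is shown, and return them sealed to the researcher. This lessens the influence of the setting but leaves the route unequal.

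The cost is small. The researcher's mailing route already exists for the UCG, and neither the intervention nor the sample size changes. Some ICG forms may be late or missing, which matters with 25 per group and about 10% dropout planned. Any information from these forms that pharmacists need for the end-of-study referral step must reach them separately, and the protocol should say how.

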### Study measurements and outcomes

#### *Study measurements*

Assessments will be conducted at three times points – baseline, week 1 and week 2 (Table 2). At baseline upon recruitment, participants will be assisted to complete the self-administered ‘Initial Pharmacy Visit’ questionnaires, comprise of:

• Demographic and lifestyle information, which includes sleep environment, smoking, alcohol consumption and caffeinated drinks intake, modified from the validated ‘Pharmacy Tool for Assessment of Sleep Health - POTASH’ [24].

• Health-related quality of life (HRQOL) assessment using validated WHO-Five Well Being Index (version 1998) [46,47].

• Sleep health assessment using a set of survey instruments adapted from POTASH [24]: Epworth Sleepiness Scale (ESS) [48,49], Insomnia Severity Index (ISI) [50], Multivariate Apnea Prediction Index (MAPI) [51] and International Restless Legs Syndrome Study Group (IRLSSG) [52].

• Community pharmacy survey: 14 questions using a 5-point Likert-type scale from 1 (strongly disagree) to 5 (strongly agree), and one open ended question.

**Table 2 T2:** Summary of measurements and study outcomes

**Measurements**	**Instruments**	**Group**	**T0**	**T1**	**T2**	**Outcome**	
Surveys/measuring tools							
Socio-demographic and lifestyle	Questionnaire	ICG, UCG	x				2˚
Health-related quality of life ^I,E^	WHO-5 Well-being index (1998)	ICG, UCG	x		x	1˚	
Sleep scale scores ^I,E^	ESS, ISI, MAPI, IRLSSG	ICG, UCG	x		x	1˚	
Community pharmacy survey ^I^	Questionnaire	ICG, UCG	x				2˚
Close-out survey ^E^	Questionnaire	ICG, UCG			x	1˚	2˚
Sleep parameters assessment							
SE%	Actigraph only	ICG		x	x	1˚	
TST, NWAK, SOL	Actigraph and sleep	ICG		x	x	1˚	
	diary						
Other factors that may interrupt sleep	Sleep diary only	ICG		x	x	1˚	
Pharmacy survey							
Close-out survey for pharmacy	Questionnaire	Pharmacists, pharmacy staff			x		2˚

T0 = baseline, T1 = 1 week after baseline, T2 = 2 weeks after baseline.

ICG: intervention care group; UCG: usual care group.

ESS: Epworth Sleepiness Scale; ISI: Insomnia Severity Index; MAPI: Multivariate Apnea Prediction Index; IRLSSG: International Restless Legs Syndrome Study Group.

SE%: Percentage of sleep efficiency; TST: Total sleep time per-24 hour period; NWAK: Number of nocturnal awakenings; SOL: Sleep onset latency.

1˚: Primary outcome; 2˚: Secondary outcome.

I: ‘Initial Pharmacy Visit’ Questionnaires; E: ‘End of Study’ Questionnaires.

Follow-up after one week from baseline will be conducted in the ICG only (Table 2). Assessment (pre) of sleep parameters will be obtained from the actigraph and sleep diary for these measures: (i) Sleep efficiency percentage (SE%), (ii) Total sleep time (TST) per 24-hour period (hours/day), (iii) Number of nocturnal awakenings (NWAK), and (iv) Sleep onset latency (SOL).

Follow-up at week 2 will be conducted to complete the study in both groups (Table 2). Assessment (post) of sleep parameters will be obtained from the actigraph and sleep diary, as in previous follow-up. Participants will also complete the ‘End of Study’ questionnaires, comprise of:

• HRQOL assessment using validated WHO-Five Well Being Index (version 1998).

• Sleep health assessment (consist of ESS, ISI, MAPI and IRLSSG), adapted from POTASH [24].

• A close-out survey, consisting of: (i) questionnaire on sleep-related lifestyle and behaviour changes since completing the study, (ii) self-opinion of sleep health after the study, and (iii) willingness and ability to pay if such program is offered as a service by community pharmacy.

Upon completion of the study, pharmacists and pharmacy staff will complete a self-administered questionnaire on the feasibility of the study, and opinions on the management of sleep disorders after participating in the study (Table 2).

#### *Study outcomes*

The primary outcomes (Table 2) of the study will be evaluated based on these three objectives:

1. To evaluate a community pharmacy-based ‘model of care’ to improve the management of sleep disorders in the community, by comparing:

a. Changes in HRQOL mean scores between and within the intervention care group (ICG) and usual care group (UCG) at baseline and week 2.

b. Changes in sleep scale mean scores – ESS, ISI, MAPI and IRLSSG, between and within the intervention care group (ICG) and usual care group (UCG) at baseline and week 2.

c. Changes in sleep parameter mean scores – sleep efficiency percentage (SE%), total sleep time (TST), number of nocturnal awakenings (NWAK) and sleep onset latency (SOL), between pre– and post–actigraphy sleep report data in the intervention care group (ICG).

2. To evaluate the role of actigraph as an objective sleep assessment instrument to monitor certain sleep disorders, by comparing:

a. Changes in sleep parameter mean scores –total sleep time (TST), number of nocturnal awakenings (NWAK) and sleep onset latency (SOL), between actigraphy and sleep diary at week 1 and week 2 in the intervention care group (ICG).

3. To evaluate the extended role of community pharmacists in managing sleep disorders in the community, by evaluating:

a. Participants’ opinions of sleep health at the end of the study.

b. Willingness and the amount able to pay if such programme is provided as a service in the community pharmacy.

Secondary outcomes (Table 2) to be evaluated are:

1. Participants’ opinions of the community pharmacy and opinions on the use of community pharmacy to seek help for sleep-related disorders.

2. Comparison between groups in sleep-related lifestyle and behaviours at week 2 follow-up.

3. Pharmacist and pharmacy staff opinions regarding the feasibility of the study and the management of sleep disorders in the community pharmacy after participating in the study.

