#### *Recruitment of pharmacies*

Contact information of the pharmacies will be obtained from the list of community pharmacies from publically available lists. Community pharmacies which meet the inclusion criteria will be invited to join the study by telephone and informed about the project. If the pharmacist expresses an interest, a research officer will arrange a face-to-face discussion for further explanation of the study and obtain consent. Upon agreement, the pharmacies will be assigned to either intervention or control group, based on convenience sampling.

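### Secondary outcome 2 compares lifestyle and behaviours between groups at week 2, but the lifestyle questionnaire is scheduled at baseline only and the week-2 item, as described, does not fit the outcome

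*Protocol article*

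**What the plan says.** Study outcomes lists as the second of three secondary outcomes: "Comparison between groups in sleep-related lifestyle and behaviours at week 2 follow-up".

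Study measurements describes the baseline instrument as "Demographic and lifestyle information, which includes sleep environment, smoking, alcohol consumption and caffeinated drinks intake". It belongs to the Initial Pharmacy Visit questionnaires. In Table 2 the row "Socio-demographic and lifestyle" covers both groups, is marked at T0 only and is labelled a secondary outcome.

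For week 2, Study measurements states: "Follow-up at week 2 will be conducted to complete the study in both groups". The End of Study questionnaires completed then contain the WHO-5, the sleep scales and a close-out survey. Part (i) of that survey is a "questionnaire on sleep-related lifestyle and behaviour changes since completing the study". Table 2 gives the close-out survey to both groups at T2.

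The intervention package includes a sleep diary that records sleep variables, "plus information related to sleep-hygiene, lifestyle and other factors that may interrupt sleep". Table 2 lists the diary for the intervention care group (ICG) only.

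On allocation, Recruitment of pharmacies says that "the pharmacies will be assigned to either intervention or control group, based on convenience sampling". Participants then follow the group of the pharmacy they attend.

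**The concern.** The outcome, the instrument and the timing do not line up. The outcome concerns behaviour at week 2. The instrument that measures behaviour is used only at T0, and the instrument used at week 2 asks about change over a period that, read literally, starts when the study finishes.

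This matters because behaviour is what the intervention works on. The advice at the first follow-up covers sleep hygiene, lifestyle, alcohol and caffeine, and the T0 questionnaire covers much the same ground. These habits are recorded in both groups before the intervention and are not recorded again in both groups on the same instrument. With four to five pharmacies allocated by convenience, customers' habits may differ between groups from the start, so a week-2 comparison needs a week-2 measure that can be set against the T0 value.

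An analysis plan cannot repair this later. It can choose a model, but it cannot supply a T2 measurement that was not taken or change a recall period after the forms have been returned.

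**Working it through.** The plan states no figure on this point, so the check sets the parts of the article side by side.

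**1. Lifestyle sources in Table 2 and Study measurements**

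| Source | ICG | Usual care group (UCG) | Times | What it gives |
|---|---|---|---|---|
| Lifestyle questionnaire | yes | yes | T0 | habits at baseline |
| Sleep diary | yes | no | T1, T2 | habits during the two weeks, one group |
| Close-out survey, part (i) | yes | yes | T2 | self-reported change |

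Only the close-out item is taken in both groups at week 2, so it is the only possible source for the outcome.

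**2. Is the T0-only mark deliberate?** The WHO-5 and sleep-scale rows carry the superscripts for both the initial and the end-of-study questionnaires, and are marked at T0 and T2. The lifestyle row has neither the end-of-study superscript nor a T2 mark. The list of End of Study contents in the text does not include the T0 lifestyle items either. Table and text agree, so this is the stated schedule and not a lost table mark.

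**3. Does the close-out item match the outcome?**
- *Quantity.* The outcome names behaviours at a time point, and the item asks about changes. A participant with poor but unchanged habits and one with good but unchanged habits would give the same answer.
- *Period.* ICG participants fill it in at the day-15 visit that ends their participation, so the period as worded is empty. UCG participants receive it by email or mail after two weeks, so their period is empty or undefined. In neither group does it cover the intervention weeks.

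**4. What can be formed from these data?**
- T0 habits in both groups: yes.
- Week-2 habits in both groups on the T0 items: no.
- Change or baseline-adjusted comparison on the same items: no.
- Between-group comparison from the diary: no, because the UCG has none.

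**5. What would adjustment achieve if the items were repeated?** Let *D* be the between-group gap in a habit at T0 and *b* the within-group slope of the T2 value on the T0 value, with 0 ≤ *b* ≤ 1 and no intervention effect. The adjusted difference is (gap at T2) − *b* × *D*.
- If the gap shrinks in line with the slope, the gap at T2 is *bD* and the adjusted difference is *bD* − *bD* = 0. The unadjusted difference is *bD*.
- If customers of the pharmacies differ stably, the gap at T2 is *D* and the adjusted difference is *D* − *bD* = *D*(1 − *b*). The unadjusted difference is *D*.

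In both cases adjustment reduces the carried-over difference. In the second it does not remove all of it unless *b* = 1.

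**The case against.** The strongest reply has three parts.

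First, the recall phrase may be loose. The article describes the topic of the questionnaire, and the questionnaire itself is not shown. Part (ii) of the same survey also speaks of a time after the study although it is completed at week 2, so the intended meaning may be change over the course of the study. This stands as a caution: the phrase is a wording problem to correct, not proof that the printed form is faulty. It does not remove the mismatch between a change item and an outcome defined at week 2.

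Second, a reader might infer that baseline differences cannot be removed at all. The document does not support that. Both groups complete the lifestyle questionnaire at T0, and the UCG section gives a purpose: "Baseline demographic and assessments will be completed for comparisons with the ICG participants". With a usable week-2 measure, those T0 values could serve as covariates or strata. Data analysis names no adjusted comparison, but that choice may be left to an analysis plan that is not shown and is no finding here.

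Third, a reader might want to state the bias in standard deviations and compare it with what 25 per group can detect. That has no footing either. The article gives no score, spread or T0-to-T2 correlation for the lifestyle items. The 25 per group comes from comparing actigraphy with sleep diaries on sleep onset latency and total sleep time. A bias worked out for a level at week 2 would also not apply to an item that asks about change.

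As to weight, this is one of three secondary outcomes and no primary comparison depends on it. That is right and limits the severity.

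**Conclusion.** The point holds in a limited form. Secondary outcome 2 has no week-2 measure, in both groups, on the instrument used at baseline. The one shared week-2 item asks about change and, as described, does not cover the study period. No same-instrument comparison from T0 to T2 can therefore be formed, in a design where convenience allocation by pharmacy makes baseline differences plausible.

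The schedule part rests on explicit statements in Table 2 and the text. The recall-period part assumes that the questionnaire is worded as the article describes it. The impact is modest and cannot be given a number from the document. It is still worth correcting before data collection, because the missing measurement cannot be recovered afterwards.

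**What to change.** - Repeat the T0 lifestyle items in the End of Study questionnaires for both groups, with unchanged wording. In Table 2, add the T2 mark and the end-of-study superscript to the lifestyle row.
- Define secondary outcome 2 as the between-group comparison of each repeated item at week 2, adjusted for the same item at T0.
- Reword part (i) of the close-out survey so that it asks about change since joining the study, and keep it as a supporting measure.
- When reporting, note that adjustment reduces stable differences between pharmacies but may not remove them fully.

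The cost is a few extra items on a form that both groups already complete, and small edits to Table 2 and the outcome text. If the longer form is not acceptable, the minimum is to redefine the outcome as self-reported change since joining and correct the recall period. That would align outcome and instrument but would still give no T0-to-T2 comparison on the same items.
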